# Integrated children’s clinic care (ICCC) versus a self-directed care pathway for children with a chronic health condition: a multi-centre randomised controlled trial study protocol

**DOI:** 10.1186/s12887-018-1034-x

**Published:** 2018-02-19

**Keywords:** Integrated care, Care coordination, Chronic health condition, Paediatrics, Randomised controlled trial, Logic model

## Abstract

**Background:**

Children with chronic health conditions have better health-related outcomes when their care is managed in a personalised and coordinated way. However, increased demand on Australian ambulatory care hospital services has led to longer waitlist times to access specialists and appropriate intervention services; placing vulnerable children at increased risk of poorer short-term (e.g. social difficulties) and long-term (e.g. convictions) health and social outcomes. Traditional approaches to increasing frequency and service of delivery are expensive and can have minimal impact on caregiver burden. A community based service-integration approach, rather than self-directed care is proposed as increased service linkages are more likely to occur and improve the health outcomes of children with a chronic health condition.

**Methods:**

An open, unblinded, multi-centre randomised controlled trial in two Australian public hospitals. 112 children (0–16 years) fulfilling the inclusion criteria will be randomised to one of two clinical pathways for management of their chronic health condition: (1) integrated children’s care clinic (ICCC) or (2) self-directed care pathway. All children and caregivers will be interviewed at 1 week, and 3, 6 and 12 month time intervals. Primary outcome measures include the Pediatric Quality of Life (PedQOL) questionnaire, Subjective Units of Distress Scale, Child Behaviour Checklist (CBCL) and Rotter’s Locus of Control Scale. Secondary outcome measures include the total number of medical appointments, school days missed and quantity of services accessed. Our main objectives are to determine if the ICCC results in better health and economics outcomes compared to the self-directed care pathway.

**Discussion:**

The success of a health systems approach needs to be balanced against clinical, mortality and cost-effectiveness data for long-term sustainability within a publicly funded health system. A clinical pathway that is sustainable, cost-effective, provides efficient evidence-based care and improves the quality of life outcomes for children with chronic health conditions has the potential to reduce waitlist times, improve access to health services, increase consumer satisfaction; and prevent costs associated with poorly managed chronic health conditions into adulthood. This study will be the first to provide clinical and health economics data on an integrated care pathway for the management of chronic health conditions in children. On a broader scale, results from this study will help guide care coordination frameworks for children with chronic health conditions; particularly with the introduction and implementation of a National Disability Insurance Scheme (NDIS) across Australia.

**Trial registration:**

Australia and New Zealand Clinical Trials Register (ANZCTR) ACTRN12617001188325. Registered: 14th August, 2017.

**Electronic supplementary material:**

The online version of this article (10.1186/s12887-018-1034-x) contains supplementary material, which is available to authorized users.

## Background

Chronic health conditions such as Attention Deficit Hyperactivity Disorder (ADHD) and intellectual impairment (II), have prevalence rates of approximately 5% [1] and 1–3% [2] in the population, respectively. Such a demand has led to longer waitlist times to see a specialist and access appropriate services within the public health sector in Australia. In addition, poorer short-term (e.g. increased risk of mental health, social difficulties) and long-term (e.g. convictions, arrests) outcomes have been reported for vulnerable children with multiple risk factors (i.e. income, education, social support) [3]. Traditional approaches to increasing frequency and service of healthcare delivery are expensive and have been shown to have minimal impact on caregiver burden [4] and changes to caregiver perception of their reduced influence over their current circumstances, including behavioural issues and overall well-being of their children [5, 6]. Research has shown that caregivers who have higher levels of external locus-of-control may be more likely to have issues with taking action to influence their children’s behaviours [5]. There is also emerging literature that suggests that locus-of-control may act as a mediator in the relationship between parenting and the caregivers’ mental health [6]. These findings suggest that a caregivers’ locus-of-control may influence their ability to undertake services and therapies which require regular and active involvement in the management of their child’s chronic health condition and well-being. Given this context, a different approach to health care systems in the management of chronic health condition in children which includes caregiver/family involvement will likely improve both child and caregiver health and social outcomes [7].

Children with chronic health conditions have better health-related outcomes when their care is managed in a coordinated way [8]. Specifically for children with ADHD there are improvements in functional outcomes when families receive more personalized and coordinated care [9] .The Chronic Care Model [10] is the most well-known model used to address healthcare systems in the management of chronic health conditions. Improved quality of life, clinical outcomes and a reduction in health costs have been seen in adults with chronic health conditions (e.g. diabetes, heart disease, chronic obstructive pulmonary disease) when the Chronic Care Model [10] was utilised. Different components (e.g. care coordination) of the Chronic Care Model [10] have been successfully used in the management of children with asthma and ADHD [1, 11, 12]. However, further research utilising the Chronic Care Model [10] to address health care outcomes in vulnerable children with other types of developmental chronic health conditions is required.

The success of a health systems approach needs to be balanced against clinical, mortality and cost-effectiveness data for long-term sustainability within a publicly funded health system. Similar to features of the Chronic Care Model, [10] community based service-integration approaches have been shown to reduce neonatal and maternal morbidity in developing countries [13] and increase the number of service linkages for low income families in a developing country. [14] Features of community based service integration approaches include health worker visits in the community, training of community staff, health promotion, availability of resources to link into existing community services and the allocation of a case manager to the child and family. However, despite reported success in reducing morbidity and increasing access for vulnerable children in developing or low-income families, cost-effectiveness data on the community service-integration models used has not been included in study designs. Nevertheless, reduced health care system costs (e.g. reduced inpatient days, reduced out of pocket expenses) has been shown when care coordination between community and tertiary care providers is provided to children with medically complex conditions [15]. No such information is available for children with chronic health conditions. Further short and long-term health economics information, which includes financial impacts within the school, family and health care environments are required, particularly for children with chronic health conditions. Such health economics information is a gap in current literature and needs to be addressed to ensure publicly funded community service-integrated models of care are cost-effective and sustainable in the long-term.

Based on available literature and increasing financial pressures to cost-effectively sustain a public health care system for children with chronic health conditions, an integrated health care pathway which incorporates the care coordination features of the Chronic Care Model [10] and includes caregiver involvement as an essential component has the potential to improve health and social benefits in an already at risk population. The development of an Integrated Children’s Clinic Care (ICCC) pathway which incorporates features of the Chronic Care Model [10] and involvement of caregivers was developed to improve health and social benefits for children with chronic health conditions. This protocol paper outlines a randomised control trial evaluating the cost-effectiveness of the ICCC pathway. The ICCC centres around an allied health liaison officer (AHLO) facilitating key components of the Chronic Care Model [10] in primary, community and acute care facilities across two Australian health districts of varying socioeconomic status’.

## Methods

### Aims

This randomised controlled trial protocol investigates the cost-effectiveness of an integrated care pathway between hospital and primary care partnerships in improving health and social outcomes in children with chronic health conditions. More specifically, our objectives are to: (1) determine if the ICCC results in better health outcomes for children with chronic health conditions, compared to a self-directed care pathway; and (2) determine the cost-effectiveness of the ICCC using health economics data. We hypothesize that: (a) Children who access the ICCC will have improved quality of life and behavioural scores than children who access the self-directed care pathway; and (b) the ICCC pathway is more cost-effective than the self-directed care pathway.

### Study design

Open, unblinded, multi-site randomised controlled trial in two Australian public hospitals - Caboolture Hospital and Gold Coast University Hospital (GCUH) Paediatric Outpatient Clinics. The Caboolture region has a social economic index for areas (SEIFA) equivalent to 0.1%, while Gold Coast region has a SEIFA ranging from 0.01 to 0.09%.

### Participants

Children aged 0 to16 years with a newly diagnosed chronic heath condition. Inclusion criteria:

Children aged 0 to 16 years who are seen by Paediatrician at Caboolture Hospital or GCUH and newly diagnosed with a chronic health condition where community based health or family support services are part of the management plan. Chronic health conditions are expected to last more than 6 months and to produce consequences that impact on the child’s quality of life [16]. Examples of chronic health conditions include (but are not limited to): Autism Spectrum Disorder (ASD), Attention Deficit Hyperactivity Disorder (ADHD), Intellectual Impairment (II), Specific Language Impairment (SLI), Oppositional Defiance Disorder (ODD), Fetal Alcohol Spectrum Disorder (FASD), Cerebral Palsy (CP).

Exclusion criteria: Children with acute medical conditions requiring urgent intervention where community follow-up is deemed inappropriate by the treating Paediatrician and /or children with a chronic medical condition primarily managed by medical consultation alone and those conditions where hospital based multidisciplinary teams provide coordinated care. Examples of excluded chronic health conditions include: cancer, cystic fibrosis, asthma and epilepsy.

### Recruitment

Children attending paediatric outpatient clinics with the Paediatrician at Caboolture Hospital or GCUH will be approached to participate in the study at the conclusion of their medical appointment by the Allied Health Liaison Officer (AHLO). The caregivers will be provided with a parent information sheet (Additional file 1) and study brochure and informed consent will be gained at this time with or as close as possible to this time. The researcher will verbally explain the caregiver information sheet, study brochure and consent form for all caregivers of eligible participants. If parents/caregivers consent for their family to be part of the study, then they will be asked to sign the consent form and initial and date each page of the caregiver information sheet and study brochure to acknowledge that they have understood the study requirements. When necessary, particularly for children of non-English speaking backgrounds, interpreter services will be used to aid in providing informed consent.

For caregivers who identify with literacy issues, the AHLO will ensure extra time is used to explain the study and obtain informed consent. [17] Before finalising consent, the AHLO will be required use the “teach back” method and ask the caregiver to explain in their own words what the research study is asking them to do, including risks and processes involved [18].

It is anticipated that a high proportion of caregivers will consent to be a part of this trial; however, we anticipate a high drop-out rate due to the length of the trial, anticipated social issues and previously documented high drop-out rates in a similar study [14]. A high attrition rate (approximately 50%) has been factored into the sample size calculations below.

### Randomisation

A randomisation list, created by an independent biostatistician will be used. Block size permutation of *n* = 7 will be utilized to ensure equal distribution of participants into each pathway. Assessment allocation (ICCC versus self-directed care pathway) will be concealed in sequentially numbered opaque envelopes and assigned to enrolled children immediately after informed consent is gained to participate in the research trial by the AHLO. The envelope will be opened in front of the caregiver and child. This would mean that the caregiver, child and AHLO involved in the trial will not be blinded to group assignment. Blinding in this trial is not feasible due to the nature of the ICCC pathway (i.e. caregivers will expect a multidisciplinary appointment with a General Practitioner).

### Data collection

An outline of the trial can be found in Fig. 1. A text message will be sent to the caregiver 24 h before a planned phone review to serve as a reminder and/or provide an opportunity for the caregiver to negotiate an appropriate time/date for the phone review. It is anticipated that a text message will facilitate increased participation and reduce attrition rates over the period of the study. A maximum of 3 phone attempts will be made at any review time point.

**Fig. 1 Fig1:**
[figure not shown]
Flow diagram of randomised control trial. * Allied Health Liaison Officer (AHLO) helps family navigate: school (e.g. individual educational plan, supports), allied health (e.g. public/private), community resources (e.g. neighbourhood centre, Moreton Bay libraries), Centrelink (e.g. allowances) in conjunction with GP, Paediatrician and/or other relevant staff in community. Abbreviations: ICCC - Integrated Children’s Clinic Care, GP - General Practitioner, Peds QOL – Paediatric Quality of Life Scale, SUDS – Subjective Units of Distress Scale, PEDI – Pediatric Evaluation of Disability Inventory, CBCL - Child Behaviour Checklist, AHLO – Allied Health Liaison Officer

#### Integrated Children’s care clinic (ICCC) pathway

At one week post Paediatrician appointment, the AHLO will make contact with the child’s General Practitioner (GP) to arrange a multidisciplinary long face-to-face meeting to help facilitate recommendations by the Paediatrician. This may include access to community allied health services. The child and caregiver will be seen by the GP at the conclusion of the multidisciplinary meeting for a consult. The AHLO will complete the following with the caregiver/child post GP consult (based on 7 day period):○ Ask how many services the child is currently accessing○ Number of days caregiver missed employment○ Collect baseline demographics data (family structure, primary carer education, primary carer employment status and mental health status). Please note: if caregiver reports emotional distress, then AHLO will recommend for caregiver to see their GP for further assistance.○ Complete Pediatric Evaluation of Disability Inventory (PEDI) if child is between 6 months to 7 years.

The AHLO will contact Education Queensland to request for number of school attendance and absent days, including any formal suspensions (if applicable). The AHLO will go through the following checklist to ensure completion. Liaison with other professionals and agencies will occur, as appropriate. Each process used and outcome will be documented to guide process evaluation for the AHLO role [19]. Please refer to Fig. 2, which outlines the logic model used to guide evaluation of the role of the AHLO in this trial. The AHLO will also submit Medicare forms to obtain information on the: number of GP visits, hospital admissions and specialist appointments for the preceding 7 days. Medical Students from each hospital will call the primary caregiver to complete the Pediatric Quality of Life (Ped QOL) Child and Family Impact Modules, [20] Subjective Units of Distress Scale (SUDS) and Locus of Control Questionnaire, and the opportunity to describe any other issues or concerns that they may have regarding their child.

**Fig. 2 Fig2:**
[figure not shown]
Logic model outlining complex interactions of processes for proposed randomised control trial in the evaluation of an Allied Health Liaison Officer (AHLO). Abbreviations: AHLO – Allied Health Liaison Officer, GP – General Practitioners, Ped QOL – Pediatric Quality of Life, SUDS – Subjective Units of Distress Scale

At 3 months (+/− 14 days) post Paediatrician appointment, the AHLO will contact Education Queensland to request for number of school attendance and absent days, including any formal suspensions (if applicable). The AHLO will submit Medicare forms to obtain information on the number of GP visits, hospital admissions and specialist appointments for the preceeding timeframe between 1 week and 3 months post Paediatrician appointment. The AHLO will also help arrange a GP long face-to-face consultation appointment to review the child to check on progress of management plan in relation to the child’s chronic health condition. Finally, the AHLO will complete the following with the caregiver/child post GP consult: ask how many services the child is currently accessing, ask the caregiver how many days they had missed employment and complete the Child Behaviour Checklist (CBCL), [21] and further information that the caregiver would like to add about what issues the child and/or family might be encountering related to access to services/support.

At 6 months (+/− 14 days) post Paediatrician appointment, the AHLO will contact Education Queensland to request for the number of school attendance and absent days, including any formal suspensions (if applicable). The AHLO will also submit Medicare forms to obtain information on the number of GP visits, hospital admissions and specialist appointments for the preceeding timeframe between 3 months to 6 months post Paediatrician appointment. Finally, the AHLO will help arrange a GP long face-to-face consultation appointment to review the child. The AHLO will also call the caregiver to: ask how many services the child is currently accessing, ask how many days the caregiver missed employment and complete the CBCL [21]. Medical Students from each hospital will also call the primary caregiver to complete: Peds QOL Child and Family Impact Modules, [20] SUDS and Locus of Control Questionnaire.

At 12 months (+/− 14 days) post Paediatrician appointment, medical students from each hospital will call the primary caregiver to complete: Peds QOL Child and Family Impact Modules, [20] SUDS and Locus of Control Questionnaire.

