#### Self-directed care pathway

The procedure for self-directed care pathway is similar to ICCC, except the participants will not have access to an AHLO to: (a) coordinate GP appointments at 1 week, 3 and 6 months post Paediatrician appointment, and (b) assist with any communication and access issues that arise during the duration of the study.

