#### Outcome measures

Primary outcome measures taken at 1 week, 3, 6, 12 months include**:** PedQOL child module (Score 0 to 100; parent or child completed), [20] PedQOL family impact module (Score 0 to 100; parent completed), [20] SUDS (Score 0 to 100; parent completed), CBCL (Percentiles, parent completed) [21] and Rotter’s Locus of Control Scale (Score 0 to 23, parent completed) [22].

Secondary outcome measures taken at 1 week, 3, 6, 12 months include the number of**:** GP visits, hospital admissions**,** specialist appointments**,** absent school days, caregiver missed employment days, school suspensions including duration in days and services currently accessed at the time.

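### The AHLO, whose help is the intervention, also collects the CBCL and two secondary counts, although medical students already phone the same caregivers at most time points

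*Protocol article*

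**What the plan says.** The Background makes the AHLO the core of the intervention: "The ICCC centres around an allied health liaison officer (AHLO) facilitating key components of the Chronic Care Model". The ICCC pathway section also places the role itself under evaluation: "Each process used and outcome will be documented to guide process evaluation for the AHLO role". Under Randomisation, the AHLO assigns the envelopes and is, with caregiver and child, not blinded. The stated reason is "Blinding in this trial is not feasible due to the nature of the ICCC pathway".

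Outcome measures lists the CBCL among the primary outcomes, described as "CBCL (Percentiles, parent completed". Services accessed and caregiver missed employment days are secondary outcomes.

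The 6-month paragraph of the ICCC pathway (printed after the Fig. 2 legend) gives the collection of these items to the AHLO: "The AHLO will also call the caregiver to: ask how many services the child is currently accessing", followed by "ask how many days the caregiver missed employment and complete the CBCL". The next sentence describes a separate caller for the other scales: "Medical Students from each hospital will also call the primary caregiver to complete: Peds QOL Child and Family Impact Modules".

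The Self-directed care pathway section describes a similar procedure with two exceptions. Controls have no AHLO to coordinate GP appointments, and none to "assist with any communication and access issues that arise during the duration of the study". It does not name who collects their data.

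**The concern.** A caregiver in the ICCC arm rates the child's behaviour, and reports services used and work lost, to the person whose help is being tested. At 1 week and 3 months this happens after a GP consult that the AHLO arranged. A grateful caregiver may report fewer behaviour problems to that person than to a stranger, and the AHLO may probe or record differently knowing the arm.

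The first hypothesis under Aims covers behavioural scores as well as quality of life, and the CBCL is the behaviour scale among the primary outcomes. Missed employment bears on the economic aim. Every CBCL administration described in the pathway text is by the AHLO, so no independently collected CBCL is described against which such a bias could be checked.

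A second issue lies in the control arm. If the AHLO also interviews controls, the AHLO meets families whose access problems the AHLO is not to help with. At the 3-month contact the AHLO also invites the caregiver to describe just such problems.

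**Working it through.** **Who collects what.** Tracing the ICCC pathway text by time point:

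| Time point | Asked by the AHLO | Setting of the AHLO contact (ICCC) | Student call |
|---|---|---|---|
| 1 week | services, missed employment | after the GP consult the AHLO arranged | yes: PedQOL, SUDS, Locus of Control |
| 3 months | services, missed employment, CBCL | after the GP consult the AHLO helped arrange | none described |
| 6 months | services, missed employment, CBCL | telephone | yes: same three scales |
| 12 months | none described | – | yes: same three scales |

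A separate caller therefore already reaches the caregiver at two of the three time points where the AHLO asks for outcomes. At 3 months there is none.

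**Control arm.** Data collection is not one of the two listed exceptions, so the natural reading is that the AHLO collects these items in both arms. Even so, the setting can differ at 1 week and 3 months, because only ICCC families have a GP consult arranged by the AHLO.

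**Blinding rationale.** It rests on what caregivers will expect, and covers caregiver, child and AHLO. It gives no reason why a student on the telephone could not be kept unaware of allocation, or why the AHLO should be the interviewer.

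**Number evaluable.** Sample size and statistical power gives 112 children, a difference of 15, 80% power, a 0.05 level and 50% attrition, but no SD. The point does not depend on this figure; it only supplies the n for the illustration. With an assumed SD of 20 and a two-sided test:

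- n per arm = 2 × (1.960 + 0.842)² × (20/15)² = 27.9, so 28
- total = 2 × 28 / (1 − 0.5) = 112, which matches

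The SD that gives exactly 80% power at 28 per arm is 20.03.

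**Illustration of size.** Suppose there is no true CBCL difference, but the interviewer shifts reports between arms by b SD. With n evaluable per arm and a normal two-sample test, the two-sided 5% false-positive rate is P(|Z + b√(n/2)| > 1.96).

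| b (assumed) | 28 per arm: b√14 | Rate | 56 per arm (no attrition): rate |
|---|---|---|---|
| 0.1 | 0.374 | 6.6% | 8.3% |
| 0.2 | 0.748 | 11.6% | 18.5% |
| 0.3 | 1.122 | 20.2% | 35.5% |

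The values of b come from no document. The protocol article names no test for the CBCL, so the normal test is also an assumption.

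**The case against.** The strongest reply is that the main result is already protected. The sample size rests on the quality of life scale, and the only test named for the primary objective compares quality of life measures. PedQOL is collected by students, as are SUDS and Locus of Control. This stands. A reader might infer that the trial's powered comparison is compromised; the documents do not support that.

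Second, the CBCL is parent completed and the parent knows the allocation whoever asks. This also stands. The illustrative rates charge the whole shift to the interviewer, so they are not the error that a change of interviewer would remove.

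Third, a reader might infer that all three items are biased in favour of ICCC. That is plausible for a behaviour rating but not shown for the counts. They are more factual, no favourable direction is stated for services accessed, and a trusted officer might draw out more reports rather than fewer.

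Fourth, a reader might infer that different people collect the data in the two arms, or that controls are in fact helped. The first goes against the natural reading of the Self-directed care pathway section. The second goes against its express wording, which withholds AHLO assistance. What remains is a setting that may differ and an awkward contact in the control arm.

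Last, the students are not said to be masked, and their 1-week call invites caregivers to raise other concerns, which could reveal the arm. Their advantage is separation from delivery; masking would be a further gain where it can be kept.

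None of this explains why the person delivering the intervention should collect these outcomes. The limitations in the Discussion deal with parent report, not with who conducts the interview.

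**Conclusion.** The point holds within limits. An unblinded AHLO, whose help is the intervention, collects the CBCL at 3 and 6 months and the services and missed-employment counts at 1 week, 3 and 6 months. This can introduce interviewer bias into one listed primary outcome and two secondary outcomes, most plausibly towards ICCC for the CBCL and of uncertain direction for the counts. Its size is unknown. The rates of about 7%, 12% and 20% show only what shifts of 0.1, 0.2 and 0.3 SD would do with 28 evaluable per arm, and should not be quoted as estimates. That the AHLO also interviews controls is a reading of the text, not a statement in it.

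The change should be made because the bias is partly avoidable with staff already in the trial, not because the powered outcome is at risk.

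**What to change.** Apply the following in both arms, with one script:

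- **1 week:** move the services and missed-employment questions to the existing student call.
- **6 months:** move these two questions and the CBCL to the existing student call.
- **3 months:** preferably have a student make the outcome call. Outcome measures already schedules the primary outcomes at this time point, so the call could serve those too.
- **Masking:** where feasible, keep student callers unaware of allocation and ask caregivers not to reveal it.
- **Control arm:** state who collects the outcome data.

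The AHLO keeps intervention delivery and the process records.

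The cost is protocol wording and longer student calls at 1 week and 6 months, with no new category of staff. The 3-month call is an addition, not a swap, because the AHLO contact continues in the ICCC arm. It also adds some burden in a trial that expects about 50% attrition and allows at most three phone attempts per review. Reporting bias from unblinded caregivers would remain.
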